### Hypotheses

We hypothesize as follows:

The intervention will be feasible to implement and can effectively reach and engage women prior to pregnancy through co-designed strategies that are acceptable to women and the implementation partner with demonstrated cost-effectiveness.Participation and engagement with intervention resources will be greater for participants who complete the intended intervention dose compared with those who do not.The intervention will improve preconception and pregnancy health knowledge and self-management.Phone and videoconference health coaching delivery will be equally feasible and cost-effective, yet engagement, adherence, and effectiveness will be greater with videoconference compared with phone-based health coaching.

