#### Health Coaching Sessions

Health coaches with a tertiary qualification in health sciences (ie, dietetics, nutrition, exercise physiology, or allied health) will deliver the program and aim for continuity wherever possible to maintain rapport. The purpose of the individual health coaching sessions is to build rapport with participants, reiterate program objectives, enhance engagement, practice goal setting and self-management skills, support participants with lifestyle modules, and provide personalized feedback on behavior change. Any module components that have not been accessed or completed by participants at the point of health coaching will be flagged for completion by the participant during or after the session.

All participants will be offered 2 personalized preconception health coaching sessions (approximately 20 minutes in duration, delivered either be phone or videoconference according to randomization) 2 to 4 weeks after program entry and 6 weeks later.

During pregnancy, 2 additional 20-minute health coaching sessions will be scheduled (8-10 weeks gestation or 1-2 weeks after starting the pregnancy module commencement and 19-20 weeks gestation).

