### Outcome Measures

Outcome measures (Table 1) are underpinned by the RE-AIM (Reach, Effectiveness, Adoption, Implementation and Maintenance [45]). Both quantitative (recruitment and intervention delivery fidelity checklists [46]) and qualitative (semistructured interviews) data collection methods will be used (Multimedia Appendix 1 and Multimedia Appendix 2).

**Table 1 table1:** Description of outcome measures.

Outcome			Description
**Implementation feasibility (primary)**			Program evaluation and feasibility for future scale up
	Reach	Proportion of the target population that were invited and participated in the program and intervening factors	
	Implementation fidelity	Delivery according to design and any variation experienced Facilitators and barriers: identification and description of intervening events	
	Adoption of the program by the implementation partner	Contextual events or factors influencing implementation within the setting, variation in any co-design implementation component	
	Cost-effectiveness	To answer questions about overall feasibility of implementation	
**Intervention effectiveness (secondary)**			Exploratory evaluation of the effectiveness of intervention delivery across preconception and pregnancy (Figure 1)
	Participation	Adherence and engagement measures to intervention dose including health coaching sessions and web-based platform interaction including degree of module completion, frequency and duration of time spent on the platform	
	Acceptability	A set of questions relating to the influence of the program in changing health behaviors, the usefulness and relevancy of the information provided, valuable aspects of the program and areas for improvement Qualitative data analysis of insights, participation factors, intervention reach, adoption and maintenance of behavior change, intervention delivery format, and areas for improvement until thematic data saturation	
	Effectiveness	On individual health behaviors including self-reported weight, health literacy [47], self-management [48], diet [49], and physical activity [50] using validated questionnaires Collected at the start of the intervention, after preconception health coaching sessions and module, and at the start of the pregnancy module	

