#### Economic Evaluation

The economic evaluation will be designed to identify the costs associated with implementation, and the net costs to health care funders. Costs of the OptimalMe implementation package will be identified from the trial data, including the costs of platform maintenance, staff time (in providing the coaching sessions), and SMS text messages. Fixed and variable costs will be identified, allowing cost per woman to be estimated at different scales of the intervention. The net costs to health care funders will be identified by quantifying the costs associated with birth type, birth complications, neonatal intensive care unit admissions, hospital stay, and ancillary utilization. Costs to Medicare Benefits Schedule will be identified based upon item numbers [51] associated with birth type and complications. Costs to private health insurers associated with hospital stay will be identified directly from the study. Costs to public hospital funders from neonatal intensive care unit admissions or any public hospital transfers will be identified from the National Hospital Cost Data Collection produced by the Independent Hospital Pricing Authority [52]. The total cost per woman will be calculated, and generalized linear models will be utilized to identify differences in costs between delivery methods. We will use these models to estimate the net cost impacts to different funders at different levels of the population reached.

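### Hypothesis 4 predicts equal cost-effectiveness with greater effect for videoconference, but the only between-arm economic comparison stated models cost alone and cannot test it

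*Protocol article*

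**What the plan says.** The fourth hypothesis (Protocol article, Hypotheses) has two halves in one sentence: "Phone and videoconference health coaching delivery will be equally feasible and cost-effective, yet engagement, adherence, and effectiveness will be greater with videoconference" than with phone. The first half is about feasibility and cost-effectiveness, the second about engagement, adherence and effectiveness. No effect measure, ratio, threshold or margin is attached to the word equally, and nothing is said about whether the two modes will cost the same.

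Cost-effectiveness analysis is one of the listed elements of the feasibility objective (Specific Objectives). Table 1 (Outcome Measures) places cost-effectiveness under the primary outcome, with the purpose "To answer questions about overall feasibility of implementation".

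The Economic Evaluation section sets its scope as follows: "The economic evaluation will be designed to identify the costs associated with implementation, and the net costs to health care funders". Delivery costs are taken from trial data, "including the costs of platform maintenance, staff time (in providing the coaching sessions), and SMS text messages". Costs of birth type, complications, neonatal intensive care, hospital stay and ancillary services are added, and a total per woman is calculated. The comparison between arms is then that "generalized linear models will be utilized to identify differences in costs between delivery methods". The same models are to project net costs to funders at different levels of reach. No effect measure enters at any step.

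**The concern.** Cost-effectiveness relates cost to effect. Once one mode is predicted to have the greater effect, cost alone no longer settles which mode is better value. A cost model with no effect term therefore cannot support or refute the first half of the hypothesis, whatever it shows.

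Delivery mode is the only randomised contrast, and the study's aim is to inform scale-up. Suppose the trial found similar costs and a greater effect with videoconference. The two modes would then not be equally cost-effective, because videoconference would give more for the same money. The economic analysis as stated would report only the absence of a cost difference, and the advantage would not appear in it.

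**Working it through.** The article states no cost, effect size, ratio or threshold for this comparison, so there is no figure to reproduce. The check is algebraic. The phone arm is set to cost C_p = 100 and effect E_p = 1. The effect ratio R = E_v/E_p (v for videoconference) takes the assumed values 1.10, 1.25 and 1.50.

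**1. Equal average ratio.** Equality means C_v/E_v = C_p/E_p, so C_v/C_p = R. Videoconference would have to cost 1.10, 1.25 or 1.50 times as much. At equal cost, its cost per unit of effect relative to phone is 1/R:
- R = 1.10: 1/1.10 = 0.91
- R = 1.25: 1/1.25 = 0.80
- R = 1.50: 1/1.50 = 0.67

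**2. Equal net benefit.** With value λ per unit of effect, equality means C_v − C_p = λ(E_v − E_p), so C_v/C_p = 1 + λ(R − 1)/100. At R = 1.25:
- λ = 50: 1 + 50 × 0.25/100 = 1.125
- λ = 100: 1.25
- λ = 200: 1.50
- λ = 500: 2.25

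Videoconference must again cost more, but the excess is proportional to the effect only at λ = 100, the phone arm's own ratio. At equal cost the net-benefit difference is λ(R − 1), which is above zero for every R above 1.

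**3. Both modes below a threshold.** If the phrase means only that each mode is cost-effective, then with a threshold of 200, equal cost and R = 1.25, the ratios are 100 and 100/1.25 = 80. Both pass and no extra cost is needed.

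**4. Could videoconference cost more under the plan?** Yes. Sessions have the same planned length in both arms ("approximately 20 minutes in duration, delivered either be phone or videoconference according to randomization"), but they are offered, and greater adherence is predicted with videoconference. Staff time in coaching is a counted cost. If a share f of the phone cost is fixed and the rest scales with sessions attended, 25% more sessions gives C_v/C_p = f + (1 − f) × 1.25:
- f = 0: 1.25
- f = 0.25: 1.19
- f = 0.50: 1.125
- f = 0.75: 1.06

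Both halves of the hypothesis can therefore be true together. Whether the extra cost matches the extra effect is an empirical question.

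**5. What a cost-only result says.** Relative cost per unit of effect is (C_v/C_p)/R:

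| Cost ratio found | R = 1.00 | R = 1.10 | R = 1.25 | R = 1.50 |
|---|---|---|---|---|
| 1.00 | 1.00 | 0.91 | 0.80 | 0.67 |
| 1.25 | 1.25 | 1.14 | 1.00 | 0.83 |

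The same cost finding fits equal or unequal cost-effectiveness, depending on an effect that the stated model does not contain.

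**The case against.** A reader might infer that the hypothesis contradicts itself. The documents do not support that. A contradiction needs a third premise, equal cost, and the article states it nowhere. Step 4 shows a route in the plan's own terms by which videoconference could both do more and cost more. Nor must the extra cost be proportional to the extra effect; that holds for the average ratio only (steps 1 and 2).

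A reader might also infer that a null cost difference will be reported as equal cost-effectiveness, or that the choice of mode to fund rests on this hypothesis. The article gives no such decision rule. These are risks to guard against and not stated intentions.

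The lenient reading in step 3 has some force, since the first hypothesis already speaks of cost-effectiveness for the programme as a whole. It fits less well here, because the fourth hypothesis compares the two modes and no threshold is given. Even on that reading, judging whether each mode is cost-effective needs an effect to set against cost.

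The strongest objection is that an article condenses a fuller plan, and that the effect measure, margin and interval method may be set out there. That is fair, and their absence is not the complaint. What remains is a mismatch between two things the article does state: a hypothesis about cost-effectiveness between arms and a between-arm analysis of cost alone. The costed birth and neonatal events do not close the gap. They let health effects enter as money, but they leave out the effectiveness outcomes in Table 1, such as health literacy, self-management, diet and physical activity.

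**Conclusion.** The point holds in a limited form. Under a comparative reading, the fourth hypothesis is true only if videoconference costs more, and the stated cost models cannot test it or by themselves deliver the promised cost-effectiveness analysis.

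The size depends on effects the documents do not give. For assumed effect ratios of 1.10 to 1.50, a finding of equal cost would leave unseen a cost per unit of effect 9% to 33% lower with videoconference (1 − 0.91 and 1 − 0.67). The direction holds for any effect ratio above 1, under either the average ratio or net benefit. If the phrase means only that each mode is acceptable value, the two halves do not conflict, and the remaining point is that the stated comparison lacks an effect term.

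This is a should-fix matter of matching the analysis to the question. It is not a flaw in the randomised design or in data collection.

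**What to change.** 1. Reword the cost half of the fourth hypothesis. Either state it as a prediction about delivery cost per woman in the two modes, or say that each mode is cost-effective if that is what is meant.
2. Add to the Economic Evaluation section a joint between-arm analysis of incremental cost and incremental effect. Use an effectiveness outcome already in Table 1 as the effect measure, with completed coaching sessions as a secondary measure. Sessions should not be the main measure, because the hypothesis lists adherence separately from effectiveness and coaching cost rises with sessions attended.
3. Report net benefit over a range of values per unit of effect, with bootstrap 95% intervals that resample women and keep each woman's cost and effect together.
4. State that equal cost-effectiveness will not be inferred from a non-significant cost difference.

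Recruitment has begun, so the change should be dated and made before any between-arm results are seen. If a fuller plan already contains the joint analysis, only the rewording and a cross-reference are needed. No new data are required. The cost is a little extra analysis and the loss of the simple claim that the modes are equally cost-effective.

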## Methods

### Implementation

#### Design

OptimalMe is a type 3 hybrid effectiveness-implementation study [35] with an active intervention phase (2 years) and a passive observation phase (up to 5 years). Type 3 hybrid implementation designs are those in which implementation outcomes are primary, and individual or population outcomes are secondary [35]. The primary outcome of the project includes overall intervention penetration and reach and the feasibility, acceptability, adoption, and fidelity of the delivery of OptimalMe. Secondary outcomes include evaluation of individual health outcomes associated with implementation delivery mode, including knowledge, risk perception, health literacy, self-management, and health behaviors. The study design is a parallel, two-arm, randomized trial at the level of the individual utilizing a pragmatic philosophy, working within real-world conditions to assess overall effectiveness. All individuals will receive the same evidence-based lifestyle intervention, and implementation delivery methods will be compared.

#### Setting

The Australian health care system is government supported via Medicare, which provides universal free care to Australian citizens and residents (and others who are eligible) and is supported by a subsidized private health system. Private health insurance, paid by the individual, allows patients to choose hospitals and health care providers from outside of the public system, with a 12-month waiting period before some, or all, of the cost of hospital treatment is reimbursed. Overall, approximately 54% of Australian adults have a form of private health insurance [36], and 27% of births in Australia occur in private hospitals [37]. Women who give birth in private hospitals attend ambulatory private obstetric care and have limited contact with hospitals prior to delivery.

Women who upgrade private insurance to include, or join with, pregnancy and birth coverage, comprise a unique population, prospectively signaling future intention for a pregnancy. In a sample of 294 women who had recently upgraded or obtained insurance for pregnancy and birth coverage, 41% intended to conceive within the next 12 months [33].

The implementation partner in this research program is Medibank Private, which is one of Australia’s largest insurers (funding approximately 20,000 births annually). Feasibility scoping shows approximately 7800 women join with, or upgrade to, pregnancy and birth coverage with this insurer nationally each year.

#### Framework

This implementation research is underpinned by the Consolidated Framework for Implementation Research [38], which provides a pragmatic framework, informed by *translation into practice* theories, that is designed to guide complex implementation projects and generate knowledge across settings and studies [38]. The framework consists of 5 domains [38]: Domain 1 consists of the unadapted intervention to be implemented and assumes the intervention is composed of core or fundamental components, essential to efficacy, surrounded by peripheral components that are adaptable to the local context, without altering the integrity of the intervention. The adaptable components are informed by domain 2 (the outer setting, ie, policy, guidelines, population needs), domain 3 (the inner setting, ie, the organization’s structure, culture, readiness to change), and domain 4 (the individuals within the outer or inner setting involved in the intervention as influencers of implementation. The implementation process (domain 5) works across all domains to achieve implementation through an iterative change process of executing and evaluating implementation activities [38].

The fundamental core components of our intervention include theoretical underpinning; simple diet; physical activity and self-management messages; low-intensity delivery format; individual health coaching sessions focused on goal setting, problem solving, and self-management delivered by a qualified health professional; and ongoing intervention support via text messaging (Domain 1). Core components were informed by our extensive intervention evidence base [16,20,21,23] and were consistently applied to setting, population, intervention tools, resources, and delivery method and format. The integration of peripheral intervention components was undertaken to incorporate best practice clinical guidelines and systematic review lifestyle intervention evidence (Domain 2) and using an intervention co-design process with the implementation partner, Medibank Private (Domain 3) experts in obstetric and lifestyle delivery and reproductive women in this life stage (Domain 4). This included the incorporation of health education resources within the intervention and the development of a consumer-tested web-based digital platform for remote delivery and comanaged participant engagement. The efficacy of health coaching delivery methods (phone and videoconference) will be compared. A governance process has been established to enable responsive and pragmatic adaptations to peripheral components in partnership with the implementation partner (Medibank Private), yet designed and managed by the clinician academic research group (Monash University). The primary outcomes form Domain 5, which includes overall intervention feasibility, reach, acceptability, and adoption as well as fidelity of the delivery of OptimalMe as planned.

### Study

#### Design

The study will be conducted in accordance with Consolidated Standards of Reporting Trials [39] and Template for Intervention Description and Replication frameworks [40].

#### Eligibility Criteria

The target intervention population will include Medibank Private members who have joined or upgraded with pregnancy and birth coverage within the 3 months prior to recruitment (to align with likely planned conception based on insurance uptake and wait times). Eligibility criteria focus on inclusiveness and includes those who are not pregnant, who wish to conceive within 12 months of recruitment, who are aged 18 to 44 years, with any BMI, who read and speak English, and who have access to an internet-capable device will be included.

#### Sample Size

Given the implementation effectiveness study design, sample size has not been powered on a clinical outcome because the primary outcome is to determine implementation learnings to inform feasibility. Available funding enables intervention delivery to approximately 300 women, which is approximately 10% of the eligible population with intention to conceive, based on our formative research [33].

#### Randomization

Participants will be randomized to receive health coaching either by telephone or via videoconference. An external senior statistician will provide computer-generated randomization codes to the research coordinator only, who will sequentially allocate all participants but will have no role in intervention delivery. Researchers involved in intervention delivery and data collection will be blinded to the allocation sequence; however, due to the nature of the intervention, they will not be blinded to participant allocation. Researchers responsible for data analysis and reporting will be blinded to both allocation sequence and participant allocation. Randomization performed external to the implementation setting is designed to reduce bias. Due to the nature of the intervention, participants will not be blinded to group allocation.

#### Recruiting Strategy

A co-designed process, using an opt-in design, was developed with the implementation partner to facilitate Australia-wide recruitment. We will use direct email communication (approximately 500 members every month, to be varied based on response rates and historical trends in email engagement observed during specified periods, including seasonal holiday periods) to recruit women (randomly selected to receive a targeted invitation by system generated mailing lists) who meet initial eligibility criteria (insurance coverage and age) with a link to the landing page of the web-based intervention platform. The page contains introductory information about the healthy lifestyle intervention, including a video. Individuals who wish to take part will be required to confirm remaining eligibility criteria, including pregnancy status and intention to conceive within 12 months, provide informed consent electronically, and register via a digital interface. The researcher coordinator will then contact the Medibank-managed integrated voice recognition system to confirm the potential participant’s membership (using first and last name, membership ID, date of birth, and postal code) and pregnancy and birth coverage status to confirm eligibility. An email with an activation link to an account for the intervention will be sent to participants, at which time, they are randomized to 1 of the 2 coaching delivery methods. Recruitment will continue until target numbers (n=300) are reached. This pragmatic approach enables management of participant flow into the intervention and will not disqualify those who may be unaware of pregnancy status at point of recruitment or who may re-evaluate their intention to become pregnant after recruitment (Multimedia Appendix 1).

### Intervention

#### Theoretical Underpinning

This intervention is based on our previous healthy lifestyle program—HeLP-her [16,20-23,27]). HeLP-her is a low intensity, behavior change program, grounded in social cognitive theory [41]. HeLP-her is nonprescriptive and provides health coach–delivered simple messages on healthy lifestyle behaviors aligned with national dietary and physical activity guidelines [30,42,43]. These are reinforced by behavior change strategies including identifying individual health priorities and facilitators and barriers for change. Realistic achievable goals are prioritized and developed by participants, and a behavioral action plan that outlines goals and timeframes is established. Individual barriers, strategies for change, and social supports are identified and discussed, and self-monitoring is practiced and encouraged [27].

